### Processes

#### Stage 1: to explore the implementation context and co-produce the intervention

To explore the context where the implementation will take place we will carry out several mappings. These will give us the context for recruitment and implementation co-design.

They are as follows:
Mapping the potential stakeholders: Mapping of the stakeholders will be done to find out who are the key stakeholders, where they come from, and what they are looking for in relationship to the study objectives [28]. To engage the community, it is essential to map the community stakeholders (civil society organisations) as they are the gatekeepers of the community. Three levels of stakeholder mapping will be carried out, namely at macro, meso and micro levels.
*Macro-level*: Stakeholders will be identified via the existing link of PI of the project in the community through meetings with local public health or other relevant departments and CSOs and using online information. Interviews with this category of stakeholders will provide insights into implementation sustainability.*Meso-level*: A strategic community volunteer organisation mapping will be carried out to find out the relevant organisations, through which individual volunteers will be selected. This will be done in three ways; using online searches, personal contacts and snowballing. In-depth interviews will be conducted to co-design a sustainable intervention implementation.*Micro-level*: An exploration will be undertaken with volunteers and end-user groups to co-design an acceptable and feasible intervention implementation.Mapping the context: social mapping will be carried out to explore the lifestyle context of the community via observations.Training of volunteers by professional health trainers and researchers following the current NICE Public health guideline [PH6] ‘Behaviour change: general approaches’ [29].CVD risk profiling by trained community health volunteers (CHV) during the pre-implementation stage.

CHVs will be the persons who have been involved in health-related volunteering for example volunteers who worked in cancer prevention, health check, healthy lifestyle etc. programme. They will be involved in the screening of the CVD risk population and implement the designed intervention.

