#### Eligible population and setting

Economically disadvantaged, lower socio-economic status (SES) postcodes, will be identified using the overall Index of Multiple Deprivation [37]; Participants’ SES will be determined by their postcode of residence. Any resident aged 18 or above living in the study postcode areas will be eligible to take part in the baseline assessment for the study.
Study sample size and power calculation

The sample size calculation for the quantitative study used statistical modelling for a stepped wedge design, randomising community centres over time with the InterHEART score as the outcome (90% power for 5% significance, small effect size (Cohen’s D) = 0.25, intracluster correlation coefficient of 0.05, control clusters crossing to intervention in 4 steps, participant autocorrelation = 0.7 and cluster autocorrelation = 0.9), which requires a total of at least 144 persons. This needs approximately 200–300 people across the two sites as we expect a high level of attrition (as much as 50%). At least 1500 community members will need to be screened to achieve this recruitment [38].
(b)Recruitment of community health volunteers and trial participants

Community Health Volunteers (CHVs) will be recruited to perform CVD risk profiling assessments through a combination of ‘doorstep outreach’ and ‘intermediary organisation recruitment’ approaches in East Sussex and through existing community and neighbourhood groups with the assistance of partners such as Self-Help UK, the Renewal Trust, Nottingham CVS and others in Nottingham. For recruitment of trial participants, we will use similar community networks, and endeavour to use quota sampling, in that we will seek to ensure the inclusion of high, low and median income neighbourhood residents, citizens from the South Asian and African diasporas; and will encourage participants to refer others to the researchers who may be able to potentially contribute or participate in the study.
(c)Baseline screening of CVD risk

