In the post-intervention phase, a qualitative evaluation will be carried out during which the following implementation parameters will be assessed:
The impact on awareness of CVD risks and mitigating measures, amongst disadvantaged populations of a community-based, non-clinical, CVD risk scoring tool and education.The impact of the community based non-clinical CVD risk scoring tool and education on motivational healthy lifestyle among disadvantaged populations.The facilitators and barriers to the adoption of a community-based CVD prevention implementation programme, by target populations.The perspectives of participants regarding their experience and meaning of the intervention.

These will be explored with a subset of intervention participants using focus groups or/and in-depth interview and community mapping. Participants for the qualitative component will include adult volunteers, public health stakeholders and people within the community. The community volunteers will be selected via community organisations and public health stakeholders will be selected from the same area of the research site. Community participants for the qualitative component will be selected via the community volunteers. This post-intervention qualitative study will include purposively selected trial participants.

The number of participants for the qualitative component will be flexible. The number will be determined through the principles of saturation and diversity. However, from each site, we will aim to include at least 12 respondents and a maximum of 30 respondents from different categories [41, 42].

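### Community participants for the qualitative evaluation are reached through the volunteers who screen and coach, with no stated route to people who left, so findings on barriers and experience may over-represent engaged participants

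*Protocol article*

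**What the plan says.** The relevant text is item (e), on post-intervention qualitative evaluation, under Eligible population and setting in the protocol article.

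- **Who is studied.** After listing the parameters to be assessed, it says: "These will be explored with a subset of intervention participants using focus groups or/and in-depth interview and community mapping". It then names the informants: "Participants for the qualitative component will include adult volunteers, public health stakeholders and people within the community".
- **How they are reached.** "Community participants for the qualitative component will be selected via the community volunteers". The next sentence adds: "This post-intervention qualitative study will include purposively selected trial participants". Neither sentence says who makes the final choice or by what criteria.
- **How many.** "The number will be determined through the principles of saturation and diversity". The aim is 12 to 30 respondents per site, across the different categories of informant.
- **What is at stake.** One listed parameter is: "The facilitators and barriers to the adoption of a community-based CVD prevention implementation programme, by target populations". Another is participants' own view of the intervention.

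On the volunteers' role, Stage 1 says of the community health volunteers: "They will be involved in the screening of the CVD risk population and implement the designed intervention". The Introduction says that volunteers deliver the coaching and follow-up. Under Community adaptation, Step III gives them the problem-solving and motivational interviewing.

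The sample-size item allows for attrition of up to 50%.

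**The concern.** A volunteer can most easily introduce people with whom they are still in contact and on good terms. Someone who stopped attending, or who found the coaching unhelpful, is harder to reach by that route. The volunteers also have some stake in the result: the Discussion asks them to head off disengagement and has their sessions checked for quality.

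The missing voices matter for the question asked. Barriers to adoption are best described by people who met one. The parameter concerns the target populations in general, but the sampling sentence starts from people who received the intervention, so those who declined lie outside it. The primary outcome in item (d) is defined among people who complete the assessment and coaching, which makes the qualitative component a natural place to hear from those who did not.

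Acceptability, feasibility and scalability are stated aims in the Introduction and Stage 2. If the interviews lean towards engaged participants, the programme may look easier to adopt than it is.

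**Working it through.** The plan gives no figure for this point, so there is none to reproduce. The check is mainly a comparison of texts, followed by an illustration under a stated assumption.

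**Step 1. Are the gatekeepers the deliverers?** Item (e) reaches community participants through the community volunteers, who are themselves found through community organisations. Stage 1 recruits individual volunteers through volunteer organisations and gives them screening and delivery. The Introduction and Step III give them the coaching. The descriptions match, so the overlap is well supported.

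**Step 2. Does another sentence remove the dependence?**

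| Text in item (e) | What it secures | What it leaves open |
|---|---|---|
| Purposive selection of trial participants | Deliberate rather than convenience choice | Who selects, on what criteria, and whether leavers are included |
| Saturation and diversity | A rule for the number of respondents | Who is put forward |
| Volunteers and public health stakeholders as informants | Other viewpoints | They are included as deliverers and officials, not as recipients of coaching |

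None of the three gives a route to people who left that does not depend on the volunteers.

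**Step 3. How many leavers might there be?** The sample-size item needs 144 people and plans for 200 to 300.

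- At 50% attrition: 144 / (1 − 0.5) = 288, which is inside the planned range.
- At 200 recruits, the loss allowed for is 1 − 144/200 = 28%.

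I therefore use 28% and 50%. This treats the attrition allowance as the share of enrolled people who leave, which is an assumption.

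**Step 4. Illustration of the possible shift.** Let *a* be the share who leave and *r* the chance that a leaver is put forward relative to someone who stayed. The share of leavers among the trial participants sampled is *ar* / (*ar* + 1 − *a*). For example, with *a* = 0.5 and *r* = 0.25: 0.125 / (0.125 + 0.5) = 20%. With *a* = 0.28 and *r* = 0.25: 0.07 / (0.07 + 0.72) = 9%.

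| *r* (assumed) | Share, *a* = 28% | Share, *a* = 50% | Expected leavers in 12, *a* = 50% | Expected leavers in 30, *a* = 50% |
|---|---|---|---|---|
| 1 | 28% | 50% | 6.0 | 15.0 |
| 0.5 | 16% | 33% | 4.0 | 10.0 |
| 0.25 | 9% | 20% | 2.4 | 6.0 |
| 0.1 | 4% | 9% | 1.1 | 2.7 |
| 0 | 0% | 0% | 0 | 0 |

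The documents give no value of *r*. The last two columns treat all 12 or 30 respondents at a site as trial participants, so they are upper limits: volunteers and stakeholders also count towards those numbers. The row *r* = 1 is a reference point only, because a purposive sample need not be proportional.

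**The case against.** The other side has a good deal of force.

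- **Reaching people through volunteers is not the same as volunteers choosing them.** Item (e) uses the same form of words for finding volunteers through organisations. A reader might infer that the volunteers alone decide who is interviewed; the text does not say so. This stands, but gatekeeping by deliverers carries a similar risk.
- **Two groups may be meant.** The volunteer route may cover only people within the community, with trial participants selected purposively by someone else. The wording allows this. It also allows the reading in which the purposive sample is reached by the same route, and the article does not settle which is meant.
- **Leavers are not excluded.** People who started and left are still intervention participants. A reader might infer that the sample consists of completers, or that the findings will necessarily favour the programme. Nothing in the document supports either, so the claim can only be that they may.
- **This is not the only evidence.** Stage 1 work with end users, the trial itself, the process evaluation in all phases and researchers' attendance at sessions also bear on acceptability and feasibility. Acceptability is an aim of Stage 2 but is not in the list in item (e). It would be too strong to say that the conclusion on scalability rests on these interviews.
- **Delivery may be shared.** Core components mentions support from researchers or community health workers, so not every participant need have a volunteer coach.
- **An article leaves detail to the full protocol.** Selection criteria and strata may be given there. That is fair for the missing detail. It does not dispose of the point, because the route through the volunteers is stated in the article.

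**Conclusion.** The point holds in a limited form. The article fixes a route to community participants that runs through the people who screen and coach. It adds purposive selection of trial participants without separating it from those people, and it provides no route to leavers despite expecting attrition of up to 50%. Findings on barriers to adoption and on participants' experience may therefore over-represent engaged participants.

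The size of the bias is unknown. The illustration ranges from no shift to no leavers at all, depending wholly on an assumed *r*. The conclusion rests on two readings: that the volunteers in item (e) are those described in Stage 1, and that the volunteer route also affects how trial participants are reached. The first is well supported; the second is possible but not certain. The primary outcome, the sample size and the quantitative analysis are not affected. The change is worth making because it is cheap and protects a stated question of the evaluation.

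**What to change.** Amend the selection sentence in item (e) along these lines: *The research team, and not the volunteer who coached the person, will make the purposive selection of trial participants from the study's enrolment and follow-up records. At each site the sample will include some people who left early and, where permission to contact exists, some who were eligible but declined. Volunteers may help with introductions.*

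The records should largely exist. Item (c) under Eligible population and setting sends screening data to the University repository in real time, and Data analysis plans a participant flow diagram. The article does not show whether contact details and permission are held for people who declined, so that part is conditional.

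The cost is a change of wording, more contact attempts, and lower acceptance among people who left. The planned 12 to 30 respondents per site can stay. At the lower end, places shared with volunteers and stakeholders will be tight, so the aim should be to include some leavers at each site, not a fixed proportion.

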#### Stage 3: process evaluation of the intervention

To assess the fidelity of the conclusions concerning the project’s effectiveness, ongoing assessment, monitoring, and enhancement is important. If significant intervention effects are observed, but fidelity was not assessed, it cannot be determined if the effectiveness is attributable to unintentionally added or omitted components. Bellg and colleagues [43] propose that considerations of fidelity should permeate all stages of the study: design of the study, provision of training, delivery of the intervention, receipt of the intervention, and re-enactment of skills. As a result, we will carry out a process evaluation of the project. This will be reached through Process documentation of all the stages of this project including community volunteers mapping, healthy lifestyle counselling, action planning and problem-solving.

Thirsk and Clark [44] argue how health-care interventions need to be understood in ways that are responsive to the complexities and intricacies of programs, people and places. They emphasise the understanding of the comprehensive experience of the persons who are delivering and receiving the intervention. Process evaluation is a tool that can capture the intervention experience. We will be following the model designed by Moore et al. [45]; Fig. 1.

**Fig. 1 Fig1:**
[figure not shown]
Process evaluation model by Moore et al. [45]

### Data analysis

Flow of trial clusters and participants will be depicted in a CONSORT 2010 Statement flow diagram from the extension to trials randomised in clusters [46]. Quantitative data will be analysed using Stata version 16 or later [47]. Descriptive statistics will summarise outcomes before and after clusters cross over to the intervention [48]. Normally distributed variables will be summarised by means and standard deviations, skewed continuous variables by medians and interquartile ranges, categorical variables by frequencies and percentages. We will estimate the treatment effect using a cross-classified linear mixed effects model. A statistical analysis plan will be agreed and signed off prior to final analysis commencing. Thematic analysis of qualitative data will be carried out using a constant comparison method of analysis, which will gather and generate ideas and categories through inductive processes. The computer package NVivo will be used to support the primary data analysis [49]. Memo writing will be carried out to describe details of the interview setting and interaction of respondent and interviewer that may not be captured in audio transcriptions. This thematic analysis has deductive and inductive elements, lending itself to multidisciplinary health research [50]. The analysis framework will incorporate the key theoretical constructs and respond to the context of policy and practice to include a range of deductive themes. Further themes will be induced from the interview data.

An appropriate balance of integration between empirical data and interpretation will be ensured. The investigators will extract the meaning of the empirical data and interpret them whilst acknowledging the complexity of the phenomena of CVD risk reduction in the context of community engagement [51]. This method holds links to the original data and the output allows comprehensive and transparent data analysis.

## Discussion

Given that the rolling out of the NHS Health Checks programme over and above current care across the UK has not been implemented as efficiently as it could have been, especially in some of the most disadvantaged groups prone to developing CVD, the project aims to scale-up packages of interventions for cardiovascular prevention particularly to these vulnerable populations. This interdisciplinary project includes public health, social and behavioural science approaches. The main focus of this project is the de-institutionalization of health care by operating outside of formal healthcare settings. The project will place emphasis on the power of citizens, combining their efforts to generate cultures of care which complement or even compensate for the inadequacies of formal systems and are thus more sustainable. The research project will ultimately develop a community engagement-based CVD primary prevention programme to support or enhance the performance of the NHS health care.

We have considered the potential operational issues in performing the study and have carefully thought out mechanisms to mitigate these. The following potential practical challenges in implementing the project have been identified: retaining the volunteers, retaining ‍ the research participants, and maintaining the quality of goal setting and motivational interviewing for an effective behaviour change intervention. In order to retain the volunteers, we will recruit staff on a paid basis from each site to work closely with the volunteers. We will conduct risk assessment audits together with the site staff so that additional needs of the volunteers, generated by their participation in the study, can be met. The research team will liaise with the paid site staff to take steps to ensure the volunteers are engaged and enthusiastic about their role and support them when this is not the case. In order to ensure retention of the research participants, the researchers will work very closely with the volunteers. The researcher will be present in a number of motivational interviewing sessions (with participants’ consent) and become familiar with the participants’ experiences and circumstances. As the participants come from a low socio-economic background it is likely that they might drop out from the study due to other pressures in their everyday lives. We will try to identify such potential threats among the participants and encourage the volunteers to pre-empt any lack of engagement by discussing strategies for maintaining motivation with their participants. The motivational interviews will be quality checked at intervals by researchers and trainers by observing some of these sessions (with participants’ consent). A regular feedback mechanism and tailored training plan are in place to improve the interview quality when any weakness is identified. With this carefully designed risk mitigation plan we hope to make sure the project meets its goals.

With our approach of taking cardiovascular disease prevention out of formal healthcare services and bringing it into the control of people in their own communities we hope to co-design a sustainable and scalable intervention which enables members of low SES communities in the UK to take control of their cardiovascular health, and improve their quality of life.

## Data Availability

Not applicable because a protocol should not contain any data; it sets out the research questions and how they will be addressed.
